### **9.2.2 Regulatory Reporting for Studies Conducted Under DMID-Sponsored Investigational New Drug (IND) Application**

Following notification from the investigator, DMID, the investigational new drug (IND) sponsor, will report events that are both serious and unexpected events that are related to study

product(s) to the FDA within the required timelines as specified in 21 CFR Part 312 Section 312.32: fatal and life-threatening events within 7 calendar days (by telephone or fax). All written reports will be sent within 15 calendar days. All SAEs designated as “not related” to study product(s) will be reported to the FDA at least annually in a summary format.

### 9.2.3 Reporting of Pregnancy

Pregnancies occurring in study subjects, i.e., any pregnancy that occurs within 3 months after the last vaccination, will be documented on the Pregnancy Reporting Form provided by EMMES, and this form will be used for the pregnancy event data entry into AdvantageEDCSM. All study-mandated blood samples will be obtained and the subject will continue in follow-up for safety events. Pregnancies will be followed to pregnancy outcome pending the subject's or their partner's permission.

### 9.2.4 Type and Duration of the Follow-up of Subjects after Adverse Events

Adverse events will be followed until resolved or considered stable.

## 9.3 Halting Rules

Subject safety data will be reviewed on an ongoing basis by EMMES Corporation and through the AE reporting system. Reactogenicity and safety laboratory data will be entered into the EMMES Corporation AdvantageEDCSM at the study site within 2 business days of data acquisition (e.g., receiving the laboratory reports). If any of the following halting rules criteria are met after vaccination, then enrollment and vaccinations will be stopped and data will be reviewed. The EMMES Corporation data management personnel will monitor the occurrence of the events listed below and notify the investigators and NIH/NIAID/DMID if any of the stopping criteria are met. The DMID Medical Monitor, in consultation with the investigators and site ISM, will determine whether the SMC should review the event. When directed by DMID, The EMMES Corporation and study investigators will provide information relevant to the event and affected individual to the SMC electronically for a rapid review/assessment to be completed within 24 hours. The SMC will provide feedback regarding the relatedness to vaccine and recommendations regarding how to proceed (e.g., continue enrollment and vaccinations without further review, formal halt and/or *ad hoc* meeting of the SMC). If the SMC review cannot be secured within 24 hours, the study will be halted until SMC review. A decision to proceed or to terminate enrollment, vaccinations, or the trial will be made in consultation with the SMC (including the independent safety monitor), the NIH/NIAID/DMID, and the clinical investigators.

During the study, if the criteria to halt are met, but it is determined that the study may proceed, it is possible that additional events satisfying the same criteria will occur. In this situation, the review process described in the preceding paragraph will be initiated. For example, if two subjects experience events satisfying criterion #3 (below), but upon review the study is

permitted to proceed, only one subject need experience an event satisfying this criterion subsequently to initiate a review described in the preceding paragraph.

If the SMC determines that it is safe to resume the study, but the subject who has already experienced events contributing to another halting rule experiences a SAE, severe AE or laboratory value that is considered by the investigators, ISM, and DMID Medical Monitor to be part of the original reported event, the study will not be halted for this event. If, however, such an event occurs and is considered by the investigators/ISM/DMID Medical Monitor/SMC to be unrelated to the prior event, the study will halt and formal SMC review will occur.

1. If 2 subjects in any single vaccine group experience severe (Grade 3) vaccination site pain/tenderness within 1 week following vaccination;
2. If 2 subjects in any single vaccine group experience moderate (Grade 2 or 3) fever that is associated with the vaccination within 1 week following vaccination;
3. If 2 subjects experience a spontaneously reported adverse event that is graded to be severe (Grade 3) or life-threatening and is associated with vaccination at any time during the follow-up period;
4. If 2 subjects experience a systemic solicited reactogenicity that is graded severe (Grade 3) (other than vaccine-related fever as defined above) within 14 days of vaccination.
5. If 1 subject experiences an SAE judged by an investigator to be associated with vaccination at any point during follow-up;
6. If 2 subjects develop a laboratory value that is considered severe (Grade 3) and that is judged to be associated with vaccination at any point during follow-up;
7. If 1 subject in any vaccine group tests positive for HIV;
8. Any report of new onset of neurologic symptoms. Any other observation occurs that, in the opinion of the PI or NIH/NIAID/DMID, results in a recommendation to halt enrollment and/or further vaccinations.

During clinic visit, the study personnel will ascertain that the reported severity of an AE by the subject meets the predefined criteria of the study of grading the severity of AEs.

If halting rules are triggered and the Internet is not available, then an immediate report will be made by phone and FAX.

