Additional discomforts of this study are those of having blood drawn from an arm vein, IM injection of the vaccine, and possible reactions to the vaccine. Drawing blood causes transient discomfort and may cause fainting. Infection at the site where blood will be drawn or where the vaccination is given is extremely unlikely, but is a potential risk. Bruising at the site of blood drawing may occur, but can be prevented or lessened by applying pressure for several minutes immediately after the blood draw. Intramuscular injection may cause injection site pain, swelling, and redness. Immediate allergic reactions to vaccine, including anaphylaxis, are in general extremely rare (approximately 1 person in 4,000,000), and might occur as a skin rash such as hives, difficulty breathing, fainting, drop in the blood pressure and death. Such reactions can usually be stopped by emergency medications administered by study personnel. Vaccine recipients may develop systemic reactions such as fever, headaches, body aches, and fatigue. These reactions are usually greatest within the first 24 to 72 hours after vaccination and last 1 to 2 days. Analgesics (e.g., aspirin or Tylenol®) and rest will generally relieve or moderate these symptoms. Other hypersensitivity reactions, including Arthus reactions resulting in large local swelling reactions, are also possible.

In the ongoing Ad35.CS.01 Phase 1 study in the U.S., after evaluation of the first 6 participants of Group D, it was noted that significant reactions (grade 3) occurred in 2 of the 6 and were considered associated with vaccination. Symptoms began in the first 8 hours following vaccination, but none occurred in the first 4 hours following vaccination. These symptoms included fever, chills, myalgia, nausea and GI side effects such as diarrhea, which occasionally lasted for several days, were self-limited, and may or may not have been related to the vaccine. In addition, two individuals, one from Group A and one from Group D, developed signs and symptoms consistent with a Grade 2 brachial plexus neuropathy that was deemed associated with vaccination. For the subject in Group A, symptoms began on the day of vaccination for both the 2nd and 3rd vaccinations but resolved within 24 hours without sequelae. For the subject in Group D, symptoms began within the first week after 2nd vaccination and were resolved by the Day 7 physical examination.

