### **3.2 Study Outcome Measures**

#### **3.2.1 Primary Outcome Measure**

- The number of subjects experiencing severe (Grade 3) solicited injection site reactions within 14 days following vaccination.
- The number of subjects experiencing severe (Grade 3) solicited systemic reactions within 14 days following vaccination.
- The number of subjects spontaneously reporting severe (Grade 3) adverse events considered associated with the vaccination at any point during the study period.
- Serious adverse events considered associated with the vaccination reported at any point during the study period.

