### 5.2 Enrollment Within Each Dosage Cohort

This study will be performed as a randomized, double-blinded, dosage-escalation study. The first dosage cohort consists of 12 subjects: 10 will receive the Ad35.CS.01 malaria vaccine while 2 will receive placebo control product. The subjects in the first cohort will be enrolled as follows: subject #1 followed by subject #2 with a minimum of a 30 minute waiting period between vaccinating subjects. This schedule will allow for assessment of immediate reactions of subject #1 prior to vaccinating subject #2. Following enrollment of subject #2, a minimum of a 2-day waiting period will be required prior to enrollment of the next four subjects. This schedule will allow for further reactogenicity assessment. The minimum 2-day waiting period will continue between each group of four subjects until the enrollment of 12 subjects into the first cohort has been met.

Following the SMC review of 14-day safety data of the first cohort, the second dosage cohort will contain 12 subjects (10 will receive Ad35.CS.01 and 2 will receive normal saline placebo control product). Six subjects will be enrolled, followed by a minimum of a 2-day waiting period before the next six subjects will be enrolled. The minimum 2 day waiting period will continue between each group of six subjects until the enrollment of 12 subjects into the second cohort has been met. This process will be repeated for the third and fourth cohorts.

Enrollment of additional subjects within any dosage cohort will not occur if a halting rule is met. Enrolled subjects who drop out of the study for any reason will not be replaced.

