#### 9.1.1 Adverse Events, Reactogenicity, Serious Adverse Events

The investigator is responsible for reporting all AEs that are observed or reported during the study, regardless of their relationship to study product. Initial vaccine reactions will be assessed for at least 30 minutes after vaccination. Subjects will be visited by the study personnel to record both solicited vaccine reactions and any unsolicited AEs. Solicited local and systemic reactions and spontaneous AEs will be collected for 14 days following vaccination.

Solicited systemic reactions will include the following: headache, malaise, myalgia, fever, chills, nausea and vomiting. Solicited local injection site reactions will include the following: induration or swelling, erythema (redness), pain/tenderness, and ecchymosis or bruising.

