### Local Reactions – Injection Site Reactogenicity

Reactogenicity events are AEs that are known to occur with this type of vaccine. Reactogenicity will be analyzed using the following grading systems:

| Local Reaction       | Mild (Grade 1)                                 | Moderate (Grade 2)                      | Severe (Grade 3)                  |
|----------------------|------------------------------------------------|-----------------------------------------|-----------------------------------|
| Pain/Tenderness      | Does not interfere with activity               | Interferes with activity                | Prevents daily activity           |
| Erythema/Redness*    | >0 – 5 cm and does not interfere with activity | 5.1 – 10 cm or interferes with activity | >10 cm or prevents daily activity |
| Induration/Swelling* | >0 – 5 cm and does not interfere with activity | 5.1 – 10 cm or interferes with activity | >10 cm or prevents daily activity |
| Ecchymosis/Bruising* | >0 – 5 cm and does not interfere with          | 5.1 – 10 cm or interferes with activity | >10 cm or prevents daily activity |

|  |          |  |  |
|--|----------|--|--|
|  | activity |  |  |
|--|----------|--|--|

\* Will be measured at the greatest single diameter

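### Halting rule 1 counts only Grade 3 pain/tenderness, so non-serious Grade 3 erythema, swelling or bruising without such pain reaches no halting rule that has a count

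*Protocol*

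**What the plan says.** Protocol Section 9.3 lists the criteria that stop enrollment and vaccination pending review. Rule 1 is the only one that names a local reaction: "If 2 subjects in any single vaccine group experience severe (Grade 3) vaccination site pain/tenderness within 1 week following vaccination".

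The first primary outcome in Section 3.2.1 is broader: "The number of subjects experiencing severe (Grade 3) solicited injection site reactions within 14 days following vaccination". Section 9.1.1 defines the set: "Solicited local injection site reactions will include the following: induration or swelling, erythema (redness), pain/tenderness, and ecchymosis or bruising". In the local grading table, erythema, induration/swelling and ecchymosis each have a Grade 3 of ">10 cm or prevents daily activity".

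For systemic reactions, rule 4 counts two subjects with a "systemic solicited reactogenicity that is graded severe (Grade 3) (other than vaccine-related fever as defined above) within 14 days of vaccination".

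Section 2.3.1 lists a local risk that is not mainly pain: "Other hypersensitivity reactions, including Arthus reactions resulting in large local swelling reactions, are also possible".

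Section 5.2 ties enrollment within a cohort to the rules: "Enrollment of additional subjects within any dosage cohort will not occur if a halting rule is met".

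**The concern.** Local reactogenicity is part of the primary objective, and this is the first use of the vaccine in semi-immune adults. The systemic halting rules (2 and 4) together cover every solicited systemic reaction. The local rule covers one of four solicited reactions and half of the 14-day window, and the protocol gives no reason for the difference. Large local swelling, which the protocol itself names as possible, has no counted trigger unless it is serious or comes with Grade 3 pain.

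At stake is how promptly and predictably the trial pauses. Section 9.3 says "data management personnel will monitor the occurrence of the events listed below", and a cluster of large swellings is not among the counted events. The scheduled SMC escalation review uses data from 14 days after the first dose. No scheduled SMC review is stated after doses 2 and 3, so for those doses a pause for such a cluster would depend on someone choosing to call it.

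**Working it through.** **Step 1: coverage of each rule (Section 9.3).** The protocol states no operating characteristics for these rules, so there is no figure to reproduce. The check is one of text.

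| Rule | Event counted | Takes non-serious Grade 3 erythema, swelling or ecchymosis without Grade 3 pain? |
|---|---|---|
| 1 | Grade 3 pain/tenderness, 1 week, 2 in a group | No |
| 2 | Grade 2 or 3 fever, 1 week, 2 in a group | No |
| 3 | Spontaneously reported severe associated events, 2 subjects | No, these reactions are solicited |
| 4 | Grade 3 solicited systemic reactions other than fever, 14 days, 2 subjects | No, systemic only |
| 5 | One associated serious adverse event (SAE) | Only if serious |
| 6 | Grade 3 associated laboratory value, 2 subjects | No |
| 7 | One positive HIV test | No |
| 8 | New neurologic symptoms, or any other observation in the opinion of the investigator or sponsor | By judgment, no count |

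Of the four solicited local reactions, one has a counted rule. Grade 3 pain that first appears on days 8 to 14 enters the primary outcome but not rule 1.

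**Step 2: how often the gap would matter (illustrative).** There are 10 vaccinees per group (Section 4). The rate p of Grade 3 non-pain local reactions after one dose is assumed, because the protocol gives none. With no Grade 3 pain and no SAE,

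P(at least 2 of n) = 1 − (1 − p)^n − n·p·(1 − p)^(n−1).

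| p | n = 10 | First block of six, n = 4 to 6 |
|---|---|---|
| 5% | 8.6% | 1.4% to 3.3% |
| 10% | 26.4% | 5.2% to 11.4% |
| 20% | 62.4% | 18.1% to 34.5% |
| 30% | 85.1% | 34.8% to 58.0% |

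The first block in Groups B to D has 4 to 6 vaccinees, because two of the 12 subjects receive placebo and their split by block is not stated. Rule 1 as written is met in 0% of these cases, which follows directly from assuming no Grade 3 pain.

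**Step 3: the same with some Grade 3 pain.** Let Grade 3 pain be independent of the other signs at rate r. The widened rule sees u = 1 − (1 − r)(1 − p). With r = 2% and p = 10%, u = 1 − 0.98 × 0.90 = 0.118. Then P(at least 2 of 10) is 33.4% under the widened rule and 1.6% under rule 1 as written. With r = 5% and p = 10%, u = 0.145, and the figures are 43.7% and 8.6%.

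**Step 4: extra halts from the fix.** Let q be the assumed per-dose rate of the newly counted reactions, independent over three doses. The per-subject rate is s = 1 − (1 − q)^3, the group figure is P = P(at least 2 of 10) at rate s, and the figure for any of the four groups is 1 − (1 − P)^4.

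| q | s | P, one group | Any of four groups |
|---|---|---|---|
| 0.5% | 1.49% | 0.9% | 3.7% |
| 1% | 2.97% | 3.4% | 12.9% |
| 2% | 5.88% | 11.4% | 38.3% |

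These count only pairs of newly counted reactions. A pair made of one Grade 3 pain and one swelling would add to them.

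**The case against.** The strongest reply is that this is a design choice, not an error. Nothing in the protocol requires the halting rules to mirror the primary outcome, and the thresholds differ by event on purpose: fever halts from Grade 2, one associated SAE halts, and so does any new neurologic symptom. A reader might infer an internal contradiction. The documents do not support that.

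A reader might also infer that these reactions could never stop the trial. That is too strong. An associated serious reaction meets rule 5. A reaction that prevents activity through pain is also Grade 3 pain, so it counts under rule 1 within the week. Rule 8 is itself a halting rule, so invoking it also bars further enrollment under Section 5.2. Section 9.4 expressly foresees an ad hoc SMC meeting for a non-serious associated event outside the stopping criteria, although it describes that route as one that does not itself halt the trial. Section 5.5.3 stops further doses for a subject whose event meets an exclusion criterion.

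Nor does Section 9.3 tell data staff to watch the listed events alone. It opens by saying that safety data are reviewed on an ongoing basis.

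The rates are assumed. The Grade 3 reactions described from the US trial's highest dose (2 of the first 6) were fever, chills, myalgia, nausea and gastrointestinal effects, which chiefly concern rules 2 and 4. The case for protecting the next enrollment block is also limited: blocks may be 2 days apart and data entry may take 2 business days, so at minimum spacing a wider rule might not act in time, and a longer window could not help that block.

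All of this narrows the point. What remains is that for non-serious Grade 3 erythema, swelling or bruising without Grade 3 pain, every available response rests on judgment with no count.

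**Conclusion.** The point holds in this limited form. Rule 1 takes one of the four solicited local reactions in the first primary outcome. The other three, when non-serious and without Grade 3 pain, reach no counted halting rule. Rule 8, ad hoc SMC meetings and the escalation review after dose 1 remain, and none has a numeric criterion. The contrast with rule 4 is plain on the page and unexplained.

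The size cannot be fixed from the protocol, because it gives no local reaction rates. The figures above show only what would follow at assumed rates, with independence between subjects, between doses, and between pain and the other signs. They are not evidence that such reactions are likely.

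This is an optional improvement to the safety rules. It does not affect the validity of the analysis.

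**What to change.** Reword rule 1 so that it is met when two subjects in any one vaccine group have a Grade 3 solicited injection site reaction (pain/tenderness, erythema, induration/swelling or ecchymosis) within 1 week of vaccination. Keep the count of two per group and the Section 9.3 review process unchanged. Extending the window to 14 days would match the primary outcome and rule 4, but that is the more debatable part and can be left as an option.

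No new data are needed, since these signs are already solicited and graded. The cost is extra halts: about a 4% to 13% chance of at least one across the four groups at assumed rates of 0.5% to 1% per dose, and 38% at 2%. Each goes to the existing review, with SMC assessment within 24 hours when the sponsor directs it. Two costs are not in those figures. After a cleared halt, a single further subject would trigger review again. A prolonged pause could also push doses 2 and 3 outside their windows of plus or minus 3 days.

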### Systemic Reactogenicity Events

Systemic events include signs, symptoms, and laboratory tests. These may be solicited or spontaneously reported. Grading of systemic events are as follows:

Systemic Signs: An axillary temperature of 37.5C is considered fever in adults. Fever severity will be graded as follows:

|       | Mild (Grade 1)                | Moderate (Grade 2)                | Severe (Grade 3) |
|-------|--------------------------------------|------------------------------------------|-------------------------|
| Fever | 37.8C (100°F) -
38.4°C (101.1 °F) | 38.5°C (101.2 °F) -
38.9°C (102.1 °F) | >38.9°C (102.1 °F)      |

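### Halting rule 4 exempts vaccine-related fever but counts unrelated Grade 3 fever, so judging a fever related can remove an automatic stop; the effect is modest.

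*Protocol*

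**What the plan says.** Four counting rules in Protocol section 9.3 matter here.

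- **Rule 1:** "If 2 subjects in any single vaccine group experience severe (Grade 3) vaccination site pain/tenderness within 1 week following vaccination". One group, no causality condition.
- **Rule 2:** "If 2 subjects in any single vaccine group experience moderate (Grade 2 or 3) fever that is associated with the vaccination within 1 week". One group, association required.
- **Rule 3:** "If 2 subjects experience a spontaneously reported adverse event that is graded to be severe (Grade 3) or life-threatening". Any groups, association required, no time limit within follow-up.
- **Rule 4:** two subjects in any groups with a solicited systemic reaction "graded severe (Grade 3) (other than vaccine-related fever as defined above) within 14 days of vaccination". No causality condition.

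Section 9.1.1 lists fever among the solicited systemic reactions and has every adverse event labelled associated or not associated.

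When a rule is met, "then enrollment and vaccinations will be stopped and data will be reviewed". The DMID Medical Monitor, consulting the investigators and the site's Independent Safety Monitor (ISM), "will determine whether the SMC should review the event". After a review that lets the trial continue, "only one subject need experience an event satisfying this criterion subsequently to initiate a review".

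**The concern.** A finding of relatedness normally strengthens the case for stopping. Here it can weaken it. An unrelated Grade 3 fever counts under rule 4, across all groups for 14 days. A related one moves to rule 2, which is narrower in group scope and in time and cannot combine a fever with any other reaction. Rule 1 has the same single-group limit but no causality condition, so this inversion is specific to fever.

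The stake is a stop of enrollment and vaccination that would occur under one causality label and not under the other. Fever was among the symptoms described with the Grade 3 reactions at 10^11 vp/mL in the US study (section 2.1.2). This trial gives that dosage in group D and half of it in group C.

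**Working it through.** The protocol states no operating characteristics for the halting rules, so there is no figure to reproduce.

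**Step 1: same events, label switched.** All fevers are Grade 3, isolated, solicited and non-serious; days count from vaccination. The outcomes hold whether the exemption covers all related fever or only related fever within one week.

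| Events | Fever related | Fever unrelated |
|---|---|---|
| Two fevers on day 2, different groups | no stop | stop (rule 4) |
| One fever on day 2 plus another subject's Grade 3 headache, same or different group | no stop | stop (rule 4) |
| Two fevers in one group, days 2 and 10 | no stop | stop (rule 4) |
| Two fevers in one group, both day 2 | stop (rule 2) | stop (rule 4) |

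Two related fevers in one group, both on day 10, stop the trial only under the one-week reading. Rule 3 helps only if the fever is recorded as spontaneous; section 9.1.1 says of systemic events "These may be solicited or spontaneously reported". Rule 5 needs a serious event.

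**Step 2: how often, under assumed rates.** The protocol gives no fever rates, so all rates below are assumptions. The model has four groups of 10 vaccinees (section 4), related fevers in week 1, one outcome per subject, no distinction by dose, and no other triggering event.

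Let p3 and p2 be the Grade 3 and Grade 2 fever rates, f the share of Grade 3 fevers with another Grade 3 solicited symptom, s the rate of other Grade 3 solicited symptoms without fever, and v = 1 - p2 - p3 - s. Per group:

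- A0 = v^10 + 10·p2·v^9 (nothing that a rule 4 without the exemption would count)
- I0 = 10·p3(1-f)·v^9 (one isolated Grade 3 fever)
- A1 = 10·s·v^9 + 90·s·p2·v^8 + 10·p3·f·v^9 (one event that rule 4 counts now)
- I1 = 90·s·p3(1-f)·v^8 (one of each)

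Each term allows at most one fever of Grade 2 or 3, so rule 2 is unmet. The probability of the gap is

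(A0+I0)^4 - A0^4 - 4·A0^3·I0 + 4[(A1+I1)(A0+I0)^3 - A1·A0^3].

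For p3 = p2 = 5%:

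- f = 0, s = 0: A0 = 0.542, I0 = 0.194, so 0.2936 - 0.0865 - 0.1236 = 0.083.
- f = 0.5, s = 0: I0 = A1 = 0.0969, so 0.1670 - 0.0865 - 0.0618 + 0.0394 = 0.058.
- f = 0, s = 2%: A0 = 0.437, I0 = 0.158, A1 = 0.096, I1 = 0.032. The first part is 0.036 and the bracketed part 0.076, in total 0.112.

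| Grade 3 / Grade 2 fever | f=0, s=0 | f=0.5, s=0 | f=0, s=2% | f=0.5, s=2% |
|---|---|---|---|---|
| 5% / 5% | 8.3% | 5.8% | 11.2% | 5.5% |
| 5% / 10% | 1.8% | 1.2% | 2.7% | 1.3% |
| 10% / 5% | 5.0% | 3.2% | 5.0% | 2.2% |
| 10% / 10% | 0.9% | 0.6% | 1.0% | 0.45% |

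If related fever occurs only in C (Grade 3 5%) and D (Grade 3 10%), with Grade 2 fever in 5% of both, the f=0, s=0 case is (10 × 0.05 × 0.90^9)(10 × 0.10 × 0.85^9) = 0.194 × 0.232 = 4.5%. With s = 2% it is 10.4%, or 5.3% if half of the fevers are accompanied.

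**Step 3: what the escalation review already covers.** Sections 5.2, 9.4 and 15.4 require SMC review of each cohort's 14-day data after the first dose before the next cohort starts. A dose-1 fever in A, B or C therefore reaches the SMC in any case. The model does not set these fevers aside, so its figures are too high as a measure of unreviewed events.

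**Step 4: extra stops if the exemption is deleted.** Assume the trial always resumes, groups run in sequence, and f = s = 0. An extra stop occurs when a group's first fever is Grade 3 and an earlier group already had a Grade 3 fever. The expected number is h × Σ(k=1..3)[1-(1-p3)^(10k)], with h = p3/(p2+p3) × [1-(1-p2-p3)^10].

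- 5%/5%: 0.326 × (0.401 + 0.642 + 0.785) = 0.60.
- Over the four rows of the table: 0.49 to 1.33.
- C/D only: 0.535 × 0.401 = 0.21.
- With s = 2%, by simulation: 0.59 (C/D only) to 1.85.

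Rule 2 alone already gives about 1.0 stops in the C/D-only case and 1.4 to 4.4 in the others.

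**The case against.** The best reply is that related fever has its own rule. Rule 2 is stricter within a group because Grade 2 also counts, and the parenthesis in rule 4 merely avoids counting the same fever twice. If only fevers that had met rule 2 in full were exempt, both gaps would close. But the text exempts the fever and not a criterion already met, so as worded it goes further than that purpose needs.

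The reply is stronger on consequences. A reader might infer that only discretion (rule 8's last sentence, an ad hoc SMC meeting, an ISM request) stands behind a related Grade 3 fever. The documents do not support that: the dose-1 escalation review is mandatory. What it leaves open is mainly fevers after dose 2 or 3, fevers in D, and a fever plus another Grade 3 symptom within one cohort while that cohort is still being vaccinated.

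The gap also shrinks when fever is common, because rule 2 then fires. In the US study, 2 of the first 6 at the top dosage had Grade 3 reactions. That is not a fever rate, but using 1/3 for D as an upper illustration (C 5%, Grade 2 fever 5%) gives 0.8% for fever pairs, and 1.6% with 2% other symptoms. Those reactions included chills, myalgia and nausea as well, so isolated Grade 3 fever may be the less common form.

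Finally, counting related fever within one dosage is a defensible choice in an escalation design. Deleting the exemption overrides that choice for Grade 3 fever, and this should be acknowledged.

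**Conclusion.** The inversion follows from the wording of rules 2 and 4 and needs no assumption about rates. It is limited to isolated, non-serious, solicited Grade 3 fever judged related, in the pairings shown. It does not mean that related fever never stops the trial: two in one group within a week do.

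The size is modest and rests on assumed rates: roughly 0.5-6% of trials if half of Grade 3 fevers are accompanied, up to about 11% if none are, and lower once dose-1 fevers already reviewed are set aside. A reader who compares any 2 of 40 with any 2 of 10 in one group might infer a gap near 30%. That figure (29.8% at a 5% Grade 3 rate, 21.3% at 10%) requires no Grade 2 fever and no accompanying symptoms, and nothing in the protocol supports that assumption.

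The wording is worth correcting because a safety stop should not become harder to reach when an event is attributed to the vaccine.

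**What to change.** Delete the parenthesis in rule 4 that excepts vaccine-related fever. Alternatively, replace it with: *other than fevers that have already triggered a review under rule 2*. Keep rule 2 unchanged as the stricter within-group rule for associated Grade 2 or 3 fever. Deletion is simpler for the data managers who apply the rules, and it settles what the words in the parenthesis refer to. The replacement counts fewer events, so it adds no more stops than deletion does.

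The amendment should say plainly that related Grade 3 fever then counts across groups for 14 days, as other Grade 3 solicited systemic reactions do.

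The cost is one line in a protocol amendment and no new data. Under the assumptions above, deletion adds about 0.2-1.9 stops per trial, including repeats, because one further event restarts the process after a first review. SMC review, when directed, is to be completed within 24 hours.
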